### **1.2. The Need for More Research to Develop Innovative Treatment for SBP in Adults with IDD:**

About 1-3% of adults in Canada have an intellectual and developmental disability (IDD) (1), and 20-40% of them have severe behavioural problems (SBP), including self-injurious behaviour, disruptive behaviour, or aggression (2), in the absence of a confirmed psychiatric diagnosis. These SBP are associated with emotion dysregulation, pain, and sleep problems (3). SBP are major contributors to morbidity, functional impairments, missed opportunities for learning, reduced quality of life, and burden on families, health, education and disability sectors (4).

SBP in adults with IDD are extremely difficult to treat. Although psychosocial interventions are generally considered first-line treatments per national and international guidance (5, 6), for a subgroup of people with IDD and SBP, these options are not effective. Antipsychotics and other psychotropic medications are thus prescribed for up to 70% of adults with IDD (7, 8), off-label, and with equivocal efficacy (9). Further, people with IDD, relative to those without IDD, are at a higher risk of side effects of psychotropic agents and less able to report side effects (10, 11). These side effects include weight gain, metabolic disturbances, neurological symptoms, and avoidable death (12). Finally, because of suboptimal responses to currently available medications, polypharmacy is commonly used to treat SBP in adults with IDD (8), potentially leading to more adverse events (9). Thus, innovative and safer interventions are pressingly needed for this population.

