After V 0, eligible participants will receive open-label nabilone starting with a dosage of 0.25 mg before sleep. During the dose titration phase (which could last up to 15 days), nabilone will be titrated in 0.25 mg increments every two days (with the dosing schedule "twice daily") after consultation with the study team during regular phone calls. This proposed up-titration schedule was decided based on a clinical trial of using Nabilone to treat non-motor symptoms in adults with Parkinson's disease (30). These regular phone calls will be carried out every two days during the whole dose titration phase until the participant reaches a stable dose for the open-label phase. The study team will also check whether the participants show any physical or mental changes which are believed to be attributed to AEs (based on the UKU side effect rating scale), and advise the participant and their caregivers on the next step of titration accordingly. Dose adjustments are

performed until the participant reaches the maximum permitted dose of 1 mg twice daily or experience intolerable AEs believed to be related to nabilone. If intolerable, the participant will use nabilone at the previous lower dose, entering the open label phase. Note that the suggested maximum nabilone daily dose per the product monograph is 6 mg. However, considering the vulnerability of the current target population, we choose to administer 2 mg/day at most in the current proposal following the maximum dose used in clinical trials in people with dementia (27) and Parkinson's disease (30). Moreover, nabilone is a THC analog; THC appears to reduce anxiety at low doses but becomes anxiogenic at high doses. Thus, administering nabilone at lower doses is theoretically consistent with the treatment objective for SBP.

Participants will be then on a stable, optimized nabilone dosage for four weeks, and then the trial ends with an on-site termination visit (V1). During the open-label trial phase, the study team will call the participant and their caregivers once weekly to perform a basic check-up, and to follow up with any questions or concerns from the trial processes. If there are any changes suspected to be associated with AEs, the UKU side effect rating scale will be assessed during the telephone check-up.

At V 1, the following post-treatment assessments will be completed:

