- Assessment of adverse events using the UKU side effect rating scale, examined by the researcher or investigator, to systemically investigate the physical AEs of nabilone.
- Re-measuring of vital signs (including blood pressure to check orthostatic hypotension) and weight to monitor the physical AEs of nabilone.
- Re-assessment of participants' cognitive capacity using the NIH Toolbox® Cognition Battery, to monitor any acute cognitive change (AEs) due to nabilone.
- Re-assessment of caregiver rated ABC-I, MOAS, and General Anxiety Subscale of ADAMS. CGI-S and CGI-I will be rated by the investigator to evaluate the severity and improvement of the behavioural problems after nabilone treatment. These re-assessments are implemented to fulfil the exploratory study aim of assessing behavioural changes pre- and post-treatment of nabilone.
- Re-assessment of caregiver's stress and crisis using the Stress Subscale of DASS-21 and BFDS, to investigate changes in their stress and distress after participants takes nabilone.
- Optional re-assessment of MRI Imaging for those who finish the pre-treatment MRI and are willing to receive the second wave of MRI imaging. This is to investigate the change in brain function and structure pre- and post-treatment of nabilone.

Nabilone will be tapered in 0.25 mg daily decrements to prevent acute withdrawal effects. This This proposed down-titration schedule was decided based on a conservative modification from a clinical trial of using Nabilone to treat behavioural and psychological symptoms of dementia (27). Phone calls will be held every other day during the dose-tapering phase, to check whether there are any changes which are believed to be attributed to withdrawal effects. A safety follow-up visit (S-F) will be scheduled after 2 weeks of full discontinuation from the study drug.

The study team will pick up the blister pack from Research Pharmacy, and then distribute to the participant/caregiver. Upon receipt of the nabilone supplies, an inventory will be performed and a receipt log filled out and signed by the research staff who picks up the blister pack. Designated research staff/pharmacy must count and verify that the pickup contains all the items noted in the

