#### Scales to assess adverse events related to the study medication

UKU side effect rating scale: The UKU side effect rating scale is a short and easy-to-use instrument that captures the core dimensions of side effects in patients using psychotropic medications. The UKU side effect rating scale is widely used in both research and in clinical settings (57), and is delivered by interviewing and observing the patients and their caregivers. Herein, we will adopt the UKU side effect rating scale specifically adjusted to adults with IDD, which consists of 35 items out of the original 48 items. This revised checklist seems more feasible to observe items that are concrete and objective than items based on the patients' subjective experiences (58). Approximately 20 minutes to complete.

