## **9.3. From nabilone**

Nabilone is indicated for severe nausea and vomiting associated with cancer chemotherapy and commercially available in Canada. Its use is usually safe and well tolerated, with sedation (~20%) and dry mouth (~10%) being the most commonly reported adverse events (no side effects of appetite and movement) in elderly with dementia or Parkinson's disease, or people with cancer (26-28, 30, 34). This safety profile is comparable to those reported in studies of CBD (36) and clonidine (37) (one of the medications for SBP of people with developmental disabilities) use in people with IDD, and less substantial relative to antipsychotics.

The addictive potential of nabilone is very low and unlikely (38), for its effect of less euphoria, slower onset of action, and more difficult titration compared to smoking cannabis. Nabilone has been shown to help with sustained abstinence from marijuana (39). The incidence of nabilone

induced full-blown psychotic disorder are also rare, and this propensity is only concerning in people with a personal or family history of schizophrenia, who will be excluded from this study. Although promising, no data ever showing efficacy and safety regarding nabilone in this population have been noted.

Per the product monograph and previous reports issued by the Canadian Agency for Drugs and Technologies in Health (26-28, 30, 34, 35), risks and side effects related to nabilone we are studying include:

- Drowsiness (66.0%)
- Vertigo (58.8%)
- Psychological high (38.8%)
- Dry mouth (21.6%)
- Depression (14.0%)
- Ataxia (reduced body coordination) (12.8%)
- Blurred vision (12.8%)
- Sensation disturbance (12.4%)
- Anorexia (loss of appetite) (7.6%)
- Asthenia (feeling of numbness and tingling) (7.6%)
- Headache (7.2%)
- Orthostatic hypotension (feeling dizzy when standing up) (5.2%)
- Euphoria (4.0%)
- Hallucinations (2.0%).

However, these estimates are influenced by factors such as drug dose, patient characteristics, detection technique, setting, and physician judgments, among others. Consequently, the side effects listed above are presented solely to indicate the relative frequency of adverse events reported in representative controlled clinical studies conducted to evaluate the safety and efficacy of nabilone across different situations.

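### The protocol gives its only structured adverse-event scale two different scopes and dedicates no on-treatment measure to the psychiatric and subjective reactions it lists for nabilone

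*Protocol*

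**What the plan says.** - **UKU at titration calls (Section 3.1).** The team calls every two days and checks for "any physical or mental changes which are believed to be attributed to AEs (based on the UKU side effect rating scale").
- **UKU at weekly open-label calls (Section 3.1).** The call is a basic check-up. The UKU is administered only if a change possibly related to an adverse event is already suspected. Table 1 marks the UKU in the open-label column without that condition.
- **UKU at V 1 (Section 3.1).** The purpose given is "to systemically investigate the physical AEs of nabilone". The neighbouring items assign physical effects to vital signs and weight, and cognitive effects to the NIH Toolbox. No V 1 safety item is assigned to psychiatric effects.
- **Version used (Section 3.4).** The scale "captures the core dimensions of side effects in patients using psychotropic medications". The form adapted to adults with IDD is one "which consists of 35 items out of the original 48 items", with this rationale: "This revised checklist seems more feasible to observe items that are concrete and objective than items based on the patients' subjective experiences". The retained items are not listed.
- **Listed reactions (Sections 1.4 and 9.3).** Fourteen are given. Five are psychiatric or largely subjective: psychological high 38.8%, depression 14.0%, sensation disturbance 12.4%, euphoria 4.0%, hallucinations 2.0%.
- **Other psychiatric measures.** Moss-PAS (ID), which has Depression, Mania and Psychosis subscales, is marked in Table 1 only at screening. ADAMS is restricted to General Anxiety and serves the exploratory aim.
- **Open capture (Section 12).** Adverse events are assessed at every visit and call. A log takes whatever the participant or substitute decision maker reports or the staff observe.
- **Use of the data (Sections 2 and 8).** Hypothesis 2 looks for lower adverse-event rates than in the antipsychotic literature. The safety profile is the percentage with each adverse effect.

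**The concern.** The safety half of the primary objective consists of adverse-event percentages, and those depend on what is asked, when and of whom. The V 1 text, read literally, leaves psychiatric effects outside the one structured scale. For the four stable-dose weeks, someone must first notice and raise a change before the structured questions are asked. If the retained UKU items do not cover a reaction, only the open log remains. Section 1.2 says that this population is "less able to report side effects", so an internal state such as feeling high is the kind of event that the log could miss.

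Missed events lower the percentages, and lower percentages support Hypothesis 2. The next trial would take over the same profile. Detection of emerging depressive or psychotic symptoms is also at stake: psychosis risk is the reason for excluding people with a personal or family history, and Section 12 explains that there is no independent monitoring board.

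**Working it through.** The protocol gives no figure on this point to reproduce. The power statement in Section 8 concerns the exploratory pre-post comparison and has no bearing here.

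**1. Scope of the UKU, place by place**

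| Place | Scope stated | When given |
|---|---|---|
| Section 3.1, titration calls | physical or mental | every two days |
| Section 3.1, open-label calls | not stated | only if a change is suspected |
| Section 3.1, V 1 | physical | at the visit |
| Section 3.2, V 1 and safety follow-up | adverse events, unrestricted | at the visit |
| Section 3.4 | core side-effect dimensions of psychotropic drugs | – |

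One entry is narrower than the others, and nothing explains why. This is an inconsistency. It does not show that the instrument is physical only.

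**2. Items removed.** 48 − 35 = 13. The document does not say which, so whether depression, hallucinations or the other three reactions are still asked about is open.

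**3. What else is scheduled after dosing starts.** Moss-PAS (ID) is not repeated. ADAMS covers anxiety. The NIH Toolbox covers cognition, and Section 7.2 allows it to be dropped for participants who cannot comply. ABC-I, MOAS and the CGI scales are clinical-effect outcomes. None is dedicated to the five reactions.

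**4. How many participants this could involve.** Inputs: N = 40 entering titration (Section 8) and the rates p in Section 9.3. Expected number = N × p.

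| Reaction | p | 40 × p |
|---|---|---|
| Psychological high | 0.388 | 15.5 |
| Depression | 0.140 | 5.6 |
| Sensation disturbance | 0.124 | 5.0 |
| Euphoria | 0.040 | 1.6 |
| Hallucinations | 0.020 | 0.8 |

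The chance of at least one true case of hallucinations is 1 − 0.98^40 = 0.55. These figures assume that the listed rates apply here, which Section 9.3 itself cautions against. They show scale only.

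**5. Direction of the error.** Let s be the share of true cases that reach the record. The expected reported percentage is s × p. Since s cannot exceed 1, incomplete capture only lowers the percentage. If the retained items ask about a reaction and caregivers answer well, s is near 1 and nothing is lost. The document fixes no value of s between 0 and 1, so for psychological high at the listed rate the reported figure could lie anywhere from 0% to 38.8%. The direction is known; the size is not.

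**The case against.** The case on the other side is substantial. The restriction to physical effects is attached to the UKU in one sentence only. The titration text uses the same scale for mental changes, and Section 3.4 presents it as covering the core side effects of psychotropic drugs, obtained by interviewing and observing both patient and caregiver. Section 12 adds assessment at every contact and a log that also takes what staff observe. An IDD-specific form built on observable items, with caregiver interview, is a reasonable answer to limited self-report. The NIH Toolbox is a further safety outcome for cognition.

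The listed rates are also a poor forecast. Section 9.3 says that they vary with dose, patients and detection technique. The daily maximum here is 2 mg against 6 mg in the monograph, and Section 1.4 says that psychotic symptoms were reported only in people with a personal or family history of psychosis, who are excluded.

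Most of this stands. It rules out saying that the UKU is a physical scale or that psychiatric events are certainly missed. It does not remove three facts: the V 1 wording conflicts with the titration wording, the structured questions are conditional for the four stable-dose weeks, and the log has no stated psychiatric prompt. The reference to detection technique in Section 9.3 supports stating how these events will be asked about.

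**Conclusion.** The concern holds as an inconsistency with a plausible one-directional bias. The scope of the only structured adverse-event scale is stated in two ways, its retained items are not named, and no on-treatment scale is dedicated to five reactions that the protocol itself lists. Apart from whatever mental items the UKU retains, these events rest on open reporting. Their percentages are liable to be too low, in the direction that favours Hypothesis 2.

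A reader might infer that the primary safety outcome does under-detect psychiatric effects, and might attach a number by assuming that some fraction of cases goes unreported. The document supports neither step. It does not identify the 13 removed items, it gives no detection rate, and full capture remains possible if the relevant items were kept. The counts in the working rest on the listed rates applying to 40 participants and are not estimates of missed events.

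The matter merits correction before enrolment because the remedy is small and the possible bias runs towards the study hypothesis.

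**What to change.** 1. Reconcile the titration and V 1 text in Section 3.1 so that the UKU covers physical and mental adverse events at every administration. Make the open-label mark in Table 1 agree with the text on when the scale is given.
2. List the 35 retained items in Section 3.4 or an appendix, and mark which of the 14 reactions in Section 9.3 they cover.
3. For the reactions not covered, add a short fixed checklist (present or absent, with severity). Word it for caregiver observation and, where possible, for the participant's own answer. Ask it at each titration call, each weekly open-label call, V 1 and the safety follow-up visit. If every reaction proves to be covered, the checklist is still useful at the weekly calls, where the UKU is conditional.
4. Report the solicited percentages separately from spontaneously reported events, among all who enter titration, so that any comparison with the antipsychotic literature can match the method of detection.

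**Cost.** A one-page form and a few minutes per contact with existing staff. Titration of up to 15 days with a call every two days gives about 7 calls; 4 weekly calls and 2 visits bring this to about 13 contacts per participant. Asking directly will raise the reported percentages and make Hypothesis 2 harder to support. Subjective states remain hard for a caregiver to observe, so the checklist reduces the gap but does not close it.

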### **3. RESEARCH DESIGN/METHODS/ANALYSIS**

#### **3.1. Study Design**

This study is a Phase I pre-pilot open-label trial of nabilone in adults with IDD and SBP. As shown in Figure 1, the trial first includes a screening visit (S-V) for eligibility, then a baseline visit (V 0), followed by a dose titration phase, and then a 4-week open label phase at a stable dose. At the end of the open label phase, participants will undergo a termination visit (V 1), after which nabilone will be tapered off over 8 days. And then, 2 weeks later, participants will undergo a last follow-up visit (V-F) to ensure safety.

At S-V, and before the informed consent process, the participant will be assessed for capacity to provide informed consent. If they cannot pass the competence test using the MacArthur Competence Assessment Tool for Clinical Research (MacCAT-CR), then the written informed consent will be obtained from their substitute decision maker after seeking participants' assent.

At S-V, participants will also be assessed for eligibility based on the inclusion and exclusion criteria, including SBP defined as a score  $\geq 18$  on the Aberrant Behaviour Checklist-Irritability

subscale (ABC-I) and a score  $\geq 4$  on the Clinical Global Impressions-Severity scale (41). The SBP should present with a consistent pattern with the frequency of  $\geq 1$  time per week for  $>3$  months.

If it is deemed necessary, research staff may review participants' medical charts to obtain clinically relevant information and/or additional information to confirm their eligibility. The investigator or research staff may also request information from the participant's physician.

At V 0 the following assessments will be completed:

- Clinical Global Impression – Severity scale (CGI-S) will be rated by the investigator to evaluate the severity of the behavioural problems.
- Measuring baseline vital signs and weight to monitor any AEs of nabilone.

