| Concomitant
medication                         | •                  | •                          | •         | •              | •                           | •                             | Either or              |
| Adaptive
function
(ABAS-3)                  | •                  |                            |           |                |                             |                               | Either or              |
| Compliance                                        |                    |                            |           |                | •                           |                               | Either or              |
| Safety Outcome                             |                    |                            |           |                |                             |                               |                        |
| PE, Vital signs                                   | •                  | •                          |           |                | •                           | •                             | In-person              |
| Pregnancy                                         | •                  |                            |           |                |                             |                               | In-person              |
| AEs (UKU)                                         |                    |                            | •         | •              | •                           | •                             | Either or              |
| NIH-Toolbox                                       |                    | •                          |           |                | •                           | •                             | In-person              |
| Clinical Effect Outcome                    |                    |                            |           |                |                             |                               |                        |
| Primary                             |                    |                            |           |                |                             |                               |                        |
| ABC-I                                             | •                  | •                          |           |                | •                           |                               | Either or              |

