### 3.2. Assessments and visits (Table 1):

Screening assessments for participants and their caregivers include:

- Assessment of prior medical records to collect information of previous cognitive assessment regarding IQ, status of Disability of Ontario Services (DSO), co-occurring physical and psychiatric diagnoses, medication use and potential changes.
- Assessment of capacity to make an informed consent based on both the MacArthur Competence Assessment Tool for Clinical Research (MacCAT-CR) (44) and clinical assessment (45). This will be carried out before the informed consent process and formal assessment.
- Interview of the Moss Psychiatric Assessment Schedules (Moss-PAS (ID)) to the caregiver to assess for co-occurring mental health conditions.
- The Adaptive Behavior Assessment System, Third Edition (ABAS-3), Adult Form, will measure adaptive behaviour and function.
- Measuring of vital signs, weight and height.
- Urine pregnancy test for sexually active women of child-bearing potential.
- Caregiver rated Aberrant Behavior Checklist-Irritability subscale (ABC-I) will be used to define the SBP. Clinical Global Impression – Severity scale (CGI-S) will be rated by the investigator to evaluate the severity of the behavioural problems.

Baseline (pre-treatment) assessments include:

- Measuring of vital signs and weight.
- Assessment of participants' cognitive capacity using the NIH Toolbox® Cognition Battery.
- Assessment of SBP of participants using the ABC-I and MOAS, and anxiety using the General Anxiety Subscale of the ADAMS, as reported by the caregivers.
- Assessment of caregiver's stress and crisis using the Stress Subscale of DASS-21 and BFDS.
- Exploratory assessment of autism symptoms using the Social Communication Questionnaire for Adults with Intellectual Disability (SCQ-AID).

- Optional assessment of MRI Imaging (dependent on the participant's ability to comply with the following assessments, in the opinion of the carers/parents and investigator).
- Concomitant medication

Post-treatment assessments include:

- Assessment of adverse events using the UKU side effect rating scale, examined by the researcher or investigator.
- Re-measuring of vital signs and weight.
- Re-assessment of participants' cognitive capacity using the NIH Toolbox® Cognition Battery.

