#### Other measures

1. Demographic questionnaire
2. Current and Concomitant medications (including type, dose, and duration of treatment)\*
3. Height
4. Weight
5. Vital signs (blood pressure, heart rate, and temperature)
6. Drug diary to evaluate compliance

---

\*The high dose of benzodiazepine (more than the benzodiazepine equivalent to lorazepam 2 mg daily) and other cannabinoids, which are still used 4 weeks before the start of the use of the study drug (titration phase), are not permitted. Other concurrent medications and non-medication treatments (including behavioural therapy, psychological therapy, occupational therapy, support group etc.) are permitted before and during the trial.

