## **8. SAMPLE SIZE AND DATA ANALYSIS**

To test the Hypotheses 1 and 2, we aim to enroll 40 patients to enter the dose titration phase, consistent with common sample sizes for Phase I trials (63).

We assume the attrition rate of 25% from the dose titration phase to entering the open-label phase. To test behavioural changes at the group level (Exploratory Objective), the sample size of the remaining participants (N=30) could be sufficient to detect differences with effect size Cohen's d as low as of 0.53, and at power = 0.8 and two-sided  $\alpha$ -level = 0.05 (G\*Power 3.1), which is similar to that detected in the study investigating the effects of nabilone on agitation associated with dementia (27).

Paired-t test will be used to investigate the pre- vs. post-treatment behavioural and brain changes. Exploratory analyses will be performed to determine predictors of response including baseline individual features, using logistic regression. Safety profiles will be described in the percentage of each adverse effects. For MRI measures, non-parametric tests will be used to explore the brain changes with nabilone treatment, assuming that only few participants can finish MRI scans eventually.

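### The orthostatic blood-pressure check is named only at V 1, so the protocol does not secure a postural reading before nabilone (V 0) or after it (V-F)

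*Protocol*

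**What the plan says.** Section 3.1 describes V 0 and V 1 differently. At V 0 the item is "Measuring baseline vital signs and weight to monitor any AEs of nabilone". At V 1 it is "Re-measuring of vital signs (including blood pressure to check orthostatic hypotension) and weight to monitor the physical AEs of nabilone". Section 3.1 gives no itemised list for V-F.

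Section 3.2 has its own visit lists. The baseline item is "Measuring of vital signs and weight". The post-treatment and the safety follow-up items share the same words, "Re-measuring of vital signs and weight". None of these mentions posture.

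Section 3.4, under other measures, defines "Vital signs (blood pressure, heart rate, and temperature"). Table 1 has one row, "PE, Vital signs", marked at screening, V 0, V 1 and V-F, all in person, with no separate orthostatic entry.

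Section 9.3 lists "Orthostatic hypotension (feeling dizzy when standing up) (5.2" per cent) among the risks of nabilone, and Section 1.4 gives the same rate. Section 8 states that "we aim to enroll 40 patients to enter the dose titration phase" and that safety will be described as the percentage with each adverse effect.

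**The concern.** Orthostatic hypotension is a difference between two postures, so a blood pressure taken in one position cannot show it. Staff who follow the V 1 text of Section 3.1 would look for a postural drop at that visit. Staff who follow Section 3.2, Section 3.4 or Table 1 would have no instruction to look for one at any visit.

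The trial has no control arm, so each participant's own reading before nabilone is the only internal comparator. A postural baseline missed at V 0 cannot be recovered once dosing starts. Nor can reversal be shown unless the same reading is taken at V-F, two weeks after full discontinuation.

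A drop that was already present is plausible in this population. Section 1.2 says that psychotropic drugs are prescribed for up to 70% of adults with IDD, and the footnote in Section 3.4 permits concurrent medication other than what is specifically disallowed. A drop first sought at V 1 could then be attributed to nabilone. It would enter the adverse-effect percentages that serve the primary objective, and Hypothesis 2 sets adverse-event rates against the antipsychotic literature.

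**Working it through.** There is no stated figure to reproduce, so the check is mainly a comparison of the texts.

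| Place in the protocol | V 0 | V 1 | V-F |
|---|---|---|---|
| Section 3.1 | plain vital signs | orthostatic check named | no itemised list |
| Section 3.2 | plain vital signs | plain vital signs | plain vital signs |
| Table 1 | common row | common row | common row |
| Section 3.4 definition | no posture | no posture | no posture |

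1. Orthostatic hypotension is tied to a visit measurement in one cell only. Its other mentions, in Sections 1.4 and 9.3, are side-effect lists.
2. No section says how a postural drop is to be measured, even at V 1.
3. The UKU does not fill the gap before treatment. Table 1 schedules it during titration, during the open-label phase, at V 1 and at V-F, but not at V 0.
4. V 1 is the only scheduled blood pressure on drug. Table 1 marks no vital signs in the titration or open-label columns, and Section 3.1 describes the contacts in those phases as telephone calls.

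For scale, the inputs are 40 participants entering titration and 25% attrition before the open-label phase (Section 8), and the listed rate of 5.2% (Section 9.3).

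- Expected to enter the open-label phase: 40 × (1 − 0.25) = 30.
- Expected cases: 40 × 0.052 = 2.08, and 30 × 0.052 = 1.56.
- Chance of at least one case: 1 − (1 − 0.052)^40 = 0.88, and 1 − (1 − 0.052)^30 = 0.80.
- Effect of one participant on the reported percentage: 1/40 = 2.5 points, and 1/30 = 3.3 points.

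If the listed rate applied here, the trial would probably see at least one case. With about two expected, one pre-existing drop attributed to nabilone would shift the reported percentage by roughly half of 5.2 (2.5/5.2 = 0.48) with 40 as the denominator.

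**The case against.** The strongest reply is that the protocol intends one common measurement throughout. Table 1 uses a single row for all four visits. The V 1 item is worded as a repeat of an earlier measurement, and the V 0 set is described as the baseline for monitoring adverse events. On that reading the V 1 parenthesis only gives the reason for repeating blood pressure. Section 3.2 also words V 1 and V-F identically, so like for like those two visits do not differ.

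Much of this stands. A reader might infer that no pre-drug or off-drug value will exist. The documents do not support that: blood pressure is scheduled at screening, V 0 and V-F, and a postural reading at those visits is left unspecified, not excluded. But a baseline that depends on staff inferring posture from a later visit's parenthesis is not secured.

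A reader might also infer that pre-existing drops will be counted as nabilone adverse events. That does not follow either. Under Section 12 the principal investigator judges the relationship of each event to the drug, and start and resolution dates are logged. Section 3.3 excludes clinically significant or unstable cardiovascular disease and psychotropic changes within 4 weeks before study drug. The UKU is repeated at V-F. These limit the risk of misattribution, but the investigator would still judge causality without an assured postural baseline.

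Finally, the share of V 1 drops that would be background cannot be estimated. The protocol gives no background prevalence, and Section 9.3 cautions that its rates depend on dose, patients and detection technique and show only relative frequency. A rate of reported reactions is not the same quantity as a prevalence of measured drops.

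**Conclusion.** The point holds as a gap in how a safety measurement is specified. The protocol names an orthostatic check at the one on-drug visit with a scheduled blood pressure and does not secure the same reading before or after nabilone. The consequence is a possible misattribution, not a demonstrated one.

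Its size is small in absolute terms: about 2 expected cases among 40, or 1.6 among 30, if the listed 5.2% carries over to this population and this method of detection. That is an assumption, and the figures serve only for scale. No sample size, error rate or hypothesis changes. The correction is worth making because safety is the primary objective, there is no control arm, the reaction is a listed one, and a missed baseline cannot be obtained later.

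**What to change.** Reconcile Sections 3.1, 3.2, 3.4 and Table 1 so that all four state the same blood-pressure measurement, lying (or seated) and then standing, by the same method at V 0, V 1 and V-F. Report the orthostatic drops at V 1 that are new relative to V 0, with their status at V-F, and give the number of participants who have readings at both V 0 and V 1.

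The cost is a few minutes at each of three visits where vital signs are already taken in person. Some participants may not cooperate with standing readings. Those readings should be recorded as missing, not replaced by a single-position value.
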